### Study aims

RESCUE + PE will decrease emotional-numbing symptoms of PTSD relative to the PE control arm (CI + PE) primary outcomeRESCUE+PE will be feasible and acceptable to veteransTreatment engagement will be higher for the RESCUE + PE group relative to CI + PE group (i.e., higher treatment attendance rates (primary), homework completion rates, and treatment completion rates)Treatment recovery rates (as measured by PTSD diagnostic status yes/no; decreased PTSD symptom severity; and increased quality of life) will be higher for the RESCUE + PE group compared to the CI + PE group at post treatment and at 3-month follow-upParticipants randomized to RESCUE + PE will experience a decrease in PTSD numbing from pre to post treatment relative to those randomized to CI + PI

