### Sample size calculation and power analyses

For the continuous longitudinal clinical, functional, and process outcomes for Primary Aims, with 35 subjects randomized to each intervention group, we will have 85% power to detect at least a 0.3 standardized (sd units) effect size between the two intervention groups assuming three time points, and an intra-class correlation no greater than 0.5; level of significance ≤ 0.05, two-tailed. A standardized effect size of 0.35 sd (Cohen’s *d*, “small” effect) is equivalent to a raw effect size of 2.8 raw scale units for the PCL (assuming pooled sd for post-treatment PCL scores is 8.1, from preliminary data). All participants randomized to condition and having completed a baseline assessment will be included in ITT analyses.

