### Treatment effects

Treatment effects will be examined via changes on continuous measures of PTSD numbing symptoms from the CAPS-5, PCL-5, and ERNS as well as by changes on continuous CAPS-5 and PCL-5 total scores, other associated mental health outcomes (e.g., BAI, PHQ-9), and functional status/quality of life (e.g., WHODAS-II; QLI). CAPS-5 and PCL-5 emotional-numbing items will be analyzed separately based on factor analytic findings and the current hypothesis that RESCUE will specifically decrease emotional-numbing symptoms.

To evaluate pre-post treatment continuous outcome measures, HLM/mixed models will be estimated with randomized group entered as a level-2 fixed effect. Effect sizes and 95% confidence intervals will be employed in a manner consistent with accepted norms [35]. For multiple point measurement related to self-report measures, estimates of slope will also be tested. For dichotomous outcomes, rates will be assessed by chi-square comparison of between-group percentages. Diagnostic improvements will be examined by computing the percentage of treated participants who no longer meet PTSD criteria at each follow-up. Outcomes will also be evaluated using CGI-I scores at all post-treatment follow-ups (i.e., percentage of veterans receiving a CGI-I rating of 1 or 2).

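### The 85% power statement guards itself with an upper bound on the ICC, but for the pre-to-post change in the primary aim that bound marks the most favourable case, and power there is well below 85%

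*Protocol article*

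**What the plan says.** The section on sample size and power covers the continuous longitudinal outcomes of the primary aims. With 35 veterans per arm and a two-sided 5% test, it claims 85% power for a difference of 0.3 SD between arms. The condition attached to that claim is "assuming three time points, and an intra-class correlation no greater than 0.5". The section gives no formula and does not say whether the effect is an averaged group difference, a change or a slope. It then turns to another effect size, "A standardized effect size of 0.35 sd", and converts it to PCL units.

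The Study aims section labels the numbing comparison as the primary outcome and restates it by saying that the experimental arm "will experience a decrease in PTSD numbing from pre to post treatment relative to those randomized to" the control arm. The Treatment effects section says effects will be examined through changes on the numbing measures, and adds: "To evaluate pre-post treatment continuous outcome measures, HLM/mixed models will be estimated with randomized group entered as a level-2 fixed effect". Slopes are to be tested as well for self-report measures taken at several points.

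**The concern.** A power statement is safe under an upper bound on the ICC only if power rises as the ICC falls. That holds for a group mean averaged over repeated measures. It does not hold for a comparison of pre-to-post change, where a lower correlation makes the change noisier.

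If the primary comparison is the change that the aims describe, a reader would take 0.5 as the cautious end of the range when it is the optimistic end. Correcting the effect size alone, while keeping three time points and the same bound, would still print a figure that the change comparison does not reach.

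**Working it through.** **Inputs.** 35 per arm, two-sided 0.05, three time points, ICC up to 0.5, effect 0.3 SD (all from the sample-size section). Assumptions added here: equal variances and a common correlation r across time points, effects in units of the SD of a single score, no attrition.

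**Formula.** Noncentral t on 68 df, with noncentrality d × √(35/2) / √VF = 4.183 × d / √VF. The variance factor VF is:
- (1 + 2r)/3 for the mean of three time points
- 2(1 − r) for pre-to-post change
- 1 − r² for the post score adjusted for baseline
- (1 − r)/2 for a slope per interval over three points
- 1 for a single value per veteran

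**Step 1: the printed 85%.** At r = 0.5:
- Mean of three points, VF = 0.667. With d = 0.3 the noncentrality is 1.537 and power is 33%. With 0.3 taken as Cohen's f (d = 2 × 0.3 = 0.6) it is 3.074 and power is 86%.
- Slope per interval, VF = 0.25. With d = 0.3 the noncentrality is 2.510 and power is 70%. With d = 0.35 it is 2.928 and power is 82%.
- Group-by-time F test: 78% with f = 0.15 (half of 0.3) and 90% with f = 0.175 (half of 0.35).

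None of these gives 85% at the printed 0.3 SD. The first two come close only with an altered input, so the formula behind the figure cannot be identified. The second effect size in the paragraph does not settle it: 0.35 × 8.1 = 2.8 PCL units, against 0.3 × 8.1 = 2.4.

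**Step 2: direction of the bound.** As r falls, (1 + 2r)/3 falls and power rises, so an upper bound on r is conservative for the averaged mean. In contrast, 2(1 − r), 1 − r² and (1 − r)/2 all rise as r falls, so power falls.

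**Step 3: power at 0.3 SD / 0.6 SD.**

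| r | Mean of three points | Pre-to-post change | Post adjusted for baseline |
|---|---|---|---|
| 0.5 | 33% / 86% | 24% / 70% | 30% / 82% |
| 0.3 | 40% / 92% | 18% / 55% | 25% / 74% |
| 0.2 | 44% / 95% | 16% / 50% | 24% / 71% |

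For the change at r = 0.5, VF = 1, so the noncentrality is 1.255 at 0.3 SD and 2.510 at 0.6 SD. By the normal approximation, 85% power for a 0.3 SD change would need r of about 1 − (0.3/2.996)² × 35/4 = 0.91, which lies outside the stated bound.

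**Step 4: effect detectable with 85% power.** For VF = 1 it is 0.727 SD, and it scales with √VF.
- Unadjusted change: 0.73 SD at r = 0.5, 0.727 × √1.4 = 0.86 SD at r = 0.3, 0.727 × √1.6 = 0.92 SD at r = 0.2.
- Post score adjusted for baseline: 0.63, 0.69 and 0.71 SD.

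**Step 5: attendance.** Study aims marks attendance as primary within the engagement aim. With one value per veteran, VF = 1 whatever the ICC: 24% power at 0.3 SD, and 0.73 SD detectable at 85%.

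**The case against.** The strongest reply is that the article names no formula. A reader might infer that the averaged-mean formula was used by mistake. The documents do not support stating that as fact: this reading gives 33% at the printed effect, and it reaches 86% only if a quantity described in SD units is read as Cohen's f. A slope difference of 0.35 SD per interval comes nearly as close. This stands, but it does not rescue the sentence. If the contrast was an averaged mean, it is not the change in the aims. If it was a slope, power also falls with the ICC and the bound is inverted.

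A second reply is that the analysis model enters group as a level-2 fixed effect and names no group-by-time term, which could mean a group main effect. The wording does leave the contrast open. However, the same section speaks of changes and of pre-post measures, and a main effect that includes baseline would average in a time point at which randomization implies no expected difference.

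A third reply is that a mixed model can use both post-treatment assessments. A reader might infer that the bound runs the wrong way for every contrast; it does not. For a baseline-adjusted mean of the two post points, VF = (1 + r)/2 − r², and power at 0.6 SD is 94% at r = 0, 91% at 0.25 and 94% at 0.5. It is nearly flat and stays above 85%. At 0.3 SD the same contrast gives 42%, 38% and 42%, so the printed claim still fails.

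Finally, the power sentence is limited to longitudinal outcomes and may never have been meant to cover attendance. That is fair, and the point there is only to say so. It is also fair that the largest shortfalls need an unadjusted change and correlations of 0.2 to 0.3, neither of which the article specifies.

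**Conclusion.** The concern holds in this form: the stated 85% at 0.3 SD is not delivered for the pre-to-post change comparison that the aims describe, and the ICC condition attached to it gives no protection for that comparison. At the most favourable value allowed, power is 24% for the unadjusted change and 30% with baseline adjustment. If the intended effect was 0.6 SD, these become 70% and 82%, and both fall at lower correlations.

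The direction of the bound is firm for a change score, a slope and a baseline-adjusted post score, but not for every contrast a mixed model could estimate. Which formula produced 85% remains unknown. The figures assume equal variances, a common correlation and no attrition. If the effect were instead expressed in SDs of the change score, the correlation would drop out and power would be 24% or 70% throughout.

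**What to change.** Keep 35 per arm and rewrite the power paragraph:
- Name the contrast that is tested for the primary aim, and whether it is adjusted for baseline.
- Replace the claim of 85% at 0.3 SD with the power or detectable effect for that contrast. At correlation 0.5 and 85% power this is about 0.73 SD for an unadjusted change, or about 0.63 SD for a post score adjusted for baseline.
- Replace the upper ICC bound with power over an assumed range of pre-post correlations, for example 0.2, 0.3 and 0.5, and quote the unfavourable end. Simply turning the bound into a minimum of 0.5 would not do, because the article gives no source for such a minimum.
- State that attendance, one value per veteran, is not covered by the three-time-point calculation.

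The cost is wording only, with no added veterans or data. The downside is a less favourable stated figure.

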### Analytic strategy

Data screening for violations of proposed statistical methods assumptions (normality of endogenous variables, linear relations among variables, no outliers, limited missing data/appropriate method for handling missing data) will include histograms, bivariate correlations, Q-Q plots, and other diagnostic methods. Processes associated with subject attrition will be examined to determine whether a missing-at-random assumption is defensible. Data will be analyzed to determine whether missing values are correlated with any baseline values and all relevant psychometric variables will be examined between groups at the baseline point of measurement to ensure adequate randomization. Given limitations of last-observation-carried-forward (LOCF), hierarchical linear models (HLM)/mixed models will be used for ITT analyses of primary and secondary outcome variables. Statistically significant treatment-related changes will be qualified with effect-size estimation and 95% confidence interval estimation.

### Feasibility/acceptability

Feasibility and acceptability will be assessed via rates and levels of recruitment, retention, and PE homework compliance rates (engagement), feedback from therapists and outside experts, perceived treatment satisfaction, and through the thematic interview data.

### Treatment effects

Treatment effects will be examined via changes on continuous measures of PTSD numbing symptoms from the CAPS-5, PCL-5, and ERNS as well as by changes on continuous CAPS-5 and PCL-5 total scores, other associated mental health outcomes (e.g., BAI, PHQ-9), and functional status/quality of life (e.g., WHODAS-II; QLI). CAPS-5 and PCL-5 emotional-numbing items will be analyzed separately based on factor analytic findings and the current hypothesis that RESCUE will specifically decrease emotional-numbing symptoms.

To evaluate pre-post treatment continuous outcome measures, HLM/mixed models will be estimated with randomized group entered as a level-2 fixed effect. Effect sizes and 95% confidence intervals will be employed in a manner consistent with accepted norms [35]. For multiple point measurement related to self-report measures, estimates of slope will also be tested. For dichotomous outcomes, rates will be assessed by chi-square comparison of between-group percentages. Diagnostic improvements will be examined by computing the percentage of treated participants who no longer meet PTSD criteria at each follow-up. Outcomes will also be evaluated using CGI-I scores at all post-treatment follow-ups (i.e., percentage of veterans receiving a CGI-I rating of 1 or 2).

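### Emotional numbing is the primary outcome, but none of its three measures is designated primary, and attendance, under a separate aim, is also labelled primary

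*Protocol article*

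**What the plan says.** Study aims attaches the primary-outcome label to a construct: RESCUE + PE "will decrease emotional-numbing symptoms of PTSD relative to the PE control arm". It names no instrument there. The engagement aim in the same list carries a second label: "higher treatment attendance rates (primary), homework completion rates, and treatment completion rates". The last listed aim restates the numbing comparison as a change between the start and the end of treatment.

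Treatment effects then says how numbing is measured: "Treatment effects will be examined via changes on continuous measures of PTSD numbing symptoms from the CAPS-5, PCL-5, and ERNS". It adds that "CAPS-5 and PCL-5 emotional-numbing items will be analyzed separately based on factor analytic findings", without making clear whether this means separately from each other or from the total scores.

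Sample size calculation and power analyses refers to aims in the plural ("For the continuous longitudinal clinical, functional, and process outcomes for Primary Aims") and gives the only level in the article: "level of significance ≤ 0.05, two-tailed". No section ranks the numbing measures, orders or adjusts the tests, or says what follows if the measures disagree.

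**The concern.** A primary outcome has to be a measured variable. Here it is a construct with three unranked instruments, so a reader of the results cannot tell from this article which comparison was meant to decide the numbing hypothesis.

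The instruments are not interchangeable. The CAPS-5 is an interview, done at post treatment and 3 months by assessors blind to condition. The PCL-5 and ERNS are self-reports by veterans who know where they volunteer. They also differ in schedule: the PCL-5 is completed weekly, while the mid-treatment list contains neither the CAPS-5 nor the ERNS. A benefit seen only on self-report and a benefit seen on the blinded interview would mean different things, and nothing says which prevails. If each measure is tested at 0.05 and any one can be presented as the primary finding, the real error rate for the numbing claim exceeds the stated level.

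**Working it through.** **Inputs from the article**
- Level: 0.05 two-tailed (Sample size calculation and power analyses).
- Numbing measures: 3 (Treatment effects).
- Further item labelled primary: 1, attendance (Study aims).

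**Assumptions, not in the article**
- Correlation among the three numbing test statistics: 0 to 0.9.
- Correlation of the attendance test with each of them: 0 or 0.3.
- Any one significant test is enough for the claim. The article states no such rule, so the results below are conditional on it.

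**The plan's own figure.** The article says "we will have 85% power to detect at least a 0.3 standardized (sd units) effect size between the two intervention groups", "with 35 subjects randomized to each intervention group", with three time points and an intra-class correlation of at most 0.5. For the mean of three measurements the SD factor is √((1 + 2 × 0.5)/3) = 0.816, so the standardised difference is 0.3/0.816 = 0.367. A two-sample test with 35 per arm then has 33.6% power, so 85% is not reproduced on this reading. That is a separate matter and does not enter the error rates. The figure that matters here is the level: one test of one named measure at 0.05 has a 5% error rate.

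**Independent tests.** The chance of at least one false positive is 1 − (1 − 0.05)^k.
- k = 3: 1 − 0.95³ = 14.3%.
- k = 4: 1 − 0.95⁴ = 18.5%.

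**Correlated tests.** Multivariate normal test statistics with mean zero, 1,000,000 draws per setting, counting draws in which any |Z| exceeds the two-sided 5% critical value:

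| Correlation among numbing tests | Three numbing tests | Three plus attendance (correlation 0.3 to 0) |
|---|---|---|
| 0 | 14.3% | 17.9–18.5% |
| 0.3 | 13.7% | 17.4–18.0% |
| 0.5 | 12.5% | 16.4–16.9% |
| 0.7 | 10.9% | 15.0–15.4% |
| 0.9 | 8.4% | 12.6–13.0% |

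**Ratio to 5%.** Three tests: 8.4/5 = 1.7 to 14.3/5 = 2.9. Four tests: 12.6/5 = 2.5 to 18.5/5 = 3.7.

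**The case against.** This is a condensed article, and testing order and multiplicity rules are commonly left to a full protocol or analysis plan. That stands for the method of adjustment. It does not stand for the identity of the primary measure: the article sets out to state its primary outcome, stops at the construct, and then uses the label a second time.

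A reader might infer that RESCUE can be declared effective on any of four tests at about three times the stated error rate. The documents do not support that. No section says that one significant result suffices, or that all are required. Attendance leads a separate engagement aim, so a false positive there would support an engagement claim, not a numbing claim. The quoted level is given for continuous longitudinal outcomes, and no level is given for attendance. A factor of three also needs four tests and a correlation near 0.7, which is an assumption.

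A reader might also count 12 weeks and 3 months as separate numbing tests, which would give 23–27% with attendance included (correlation 0.7 to 0.3 among the numbing tests, 0.2 with attendance, 0.5 over time). The last listed aim points to the end of treatment, and Treatment effects describes mixed models with group as a fixed effect, not visit-by-visit tests, so that figure does not apply.

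Retrospective registration, together with access to interim data for the unblinded principal investigator and coordinator, might suggest a choice made after seeing results. Nothing in the article shows this. It says no interim analysis procedure was included, and the registry entry, which may already name one measure, is not shown.

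Finally, the study overview describes pilot and initial efficacy testing, where strict error control is less binding. That lowers the stakes, but the article still names a primary outcome and states efficacy hypotheses.

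**Conclusion.** The concern holds in a limited form. Emotional numbing is the primary outcome, none of its three measures is designated primary, attendance carries a second primary label under another aim, and 0.05 two-tailed is the only level, with no rule for discordant results.

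The size is conditional. If any one numbing measure could carry the numbing claim at 0.05, the false-positive chance is about 8–14% instead of 5%. If attendance could also carry the trial's claim, it is about 13–19%. Both ranges rest on assumed correlations and on a success rule that the article leaves open. The gap in what is designated primary does not depend on those assumptions.

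**What to change.** Before arm-level outcome data are examined:

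- Name one numbing measure as the single primary efficacy outcome, tested at 0.05. The CAPS-5 numbing-item score is preferable because a blinded assessor rates it after treatment. Use the 12-week contrast from the planned mixed model, which matches the start-to-end-of-treatment wording of the last aim and still fits a model over baseline, 12 weeks and 3 months.
- Make the PCL-5 numbing items and the ERNS secondary.
- Make attendance a key secondary outcome, or second in a fixed sequence, as the lead measure of the engagement aim, and reword its label accordingly.
- Bring the registry entry into line if it differs.

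Sample size, visits and data collection are unchanged; the work is in the wording. There are two costs. A positive result on a self-report measure alone would no longer support the primary claim. The power illustration, now given on the PCL, would have to be restated for the chosen measure.

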**Methods/design:**

The study will include 70 veterans with PTSD treated at a Southeastern Veterans Affairs Medical Center (VAMC). All participants in the trial receive up to 12 sessions of PE. Participants are randomly assigned 1:1 to (1) volunteer at a local animal shelter or (2) volunteer at a community agency of their choice as part of their in-vivo exposure exercises for PE. Outcomes will be examined via standard clinical interviews, self-report questionnaires, and thematic interviews.

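### For CAPS-5 numbing the pre-post model fixes no contrast that matches the stated aim; a baseline-adjusted group difference at 12 weeks should be named, at no cost

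*Protocol article*

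**What the plan says.** The treatment-effect model is given in one sentence of the Treatment effects section: "To evaluate pre-post treatment continuous outcome measures, HLM/mixed models will be estimated with randomized group entered as a level-2 fixed effect". A later sentence adds: "For multiple point measurement related to self-report measures, estimates of slope will also be tested". No time term, group-by-time term or baseline covariate is named with the first sentence.

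The stated target is change. The same section opens by saying that effects will be examined through changes on continuous numbing measures from the CAPS-5, PCL-5 and ERNS. The last of the Study aims asks for a decrease in numbing from before to after treatment relative to control. Under Assessment measures, the CAPS-5 belongs to the baseline battery that is repeated at post treatment and 3 months, and it is not in the mid-treatment list.

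In the Analytic strategy section, baseline values are used to examine missingness and for a balance check: "all relevant psychometric variables will be examined between groups at the baseline point of measurement to ensure adequate randomization". Their use as covariates is neither stated nor excluded.

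**The concern.** A level-2 group predictor in a mixed model can act on the intercept, on the slope, or on both, and the sentence does not say which. The choice matters. If baseline is one of the outcome rows and group acts only on the intercept, the coefficient is the arm difference averaged over all visits. Randomisation makes the expected difference at baseline zero, so that average understates the follow-up difference. If group acts on the slope, the coefficient is a difference in change. That answers the aim, but it uses the baseline value less efficiently than adjusting for it.

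The slope sentence covers the self-report numbing measures (PCL-5 and ERNS), though only as an addition. It does not cover the CAPS-5, which is the clinician-rated numbing measure and, after treatment, the one rated by blinded assessors. With 70 veterans, the possible readings differ up to twofold in estimated effect and nearly threefold in power.

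**Working it through.** **Inputs from the protocol article.** Sample size: "with 35 subjects randomized to each intervention group". Effect size: d = 0.3 SD, from "we will have 85% power to detect at least a 0.3 standardized (sd units) effect size between the two intervention groups". The same paragraph gives three time points, an intra-class correlation of at most 0.5, and two-sided alpha of 0.05.

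**Assumptions made here.** Correlation ρ = 0.5 between any two visits, equal variances, complete data, and the same true difference d at each follow-up. Powers use the normal approximation Φ(effect / SE − 1.96), with SE = √(2v/35), where v is the variance factor.

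**The plan's own figure.** For the mean of three time points with the full 0.3 SD at each, v = (1 + 2ρ)/3 = 0.667, SE = 0.195, and power = Φ(1.537 − 1.96) = 33.6%, not 85%. The effect detectable with 85% power is (1.960 + 1.036) × 0.195 = 0.585 SD. About 85% appears only after relabelling: 85.8% if 0.3 is read as Cohen's f (d = 0.6) for a group main effect, or 86.7% if between-person variance is dropped. That mismatch is a separate issue. It is shown here because it sets the scale for what follows.

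**One baseline and one post-treatment visit, d = 0.3**

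- Plain group effect: the estimate has expectation d/2 = 0.15; v = (1 + ρ)/2 = 0.75; SE = 0.207; power = Φ(0.725 − 1.96) = 10.8%.
- Unadjusted change or group-by-time: expectation 0.30; v = 2(1 − ρ) = 1.00; SE = 0.239; power = Φ(1.255 − 1.96) = 24.0%.
- Baseline-adjusted: expectation 0.30; v = 1 − ρ² = 0.75; SE = 0.207; power = Φ(1.449 − 1.96) = 30.5%.

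The plain group effect needs 2/(1 − ρ) = 4 times the patients of the adjusted contrast.

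**Baseline and two follow-ups, d = 0.3**

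- Plain group effect: expectation 2d/3 = 0.20; v = (1 + 2ρ)/3 = 0.667; SE = 0.195; power = Φ(1.025 − 1.96) = 17.5%.
- Baseline-adjusted mean of the two follow-ups: expectation 0.30; v = (1 + ρ)/2 − ρ² = 0.50; SE = 0.169; power = Φ(1.775 − 1.96) = 42.7%.

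**Checks.** Simulation with t tests (15,000 runs per setting) gives 10.8%, 23.6% and 29.6% for the pre-post case, and 17.2% and 41.5% for the two-follow-up case.

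**Sensitivity.** The article bounds the intra-class correlation at 0.5 but gives no value, so 0.3 to 0.7 is an assumed range.

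| Pre-post power, d = 0.3 | ρ = 0.3 | ρ = 0.5 | ρ = 0.7 |
|---|---|---|---|
| Plain group effect | 11.9% | 10.8% | 10.0% |
| Unadjusted change | 18.4% | 24.0% | 36.7% |
| Baseline-adjusted | 26.0% | 30.5% | 42.0% |

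At the paragraph's other effect size, 0.35 SD, simulated pre-post powers at ρ = 0.5 are 12.9%, 30.3% and 37.5%. The order of the three is the same in every setting shown.

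**The case against.** A reader might infer that the plan, as written, tests a group effect averaged over baseline and follow-up. The documents do not support that as fact. The sentence does not name the tested parameter and does not say that baseline is an outcome row. The opening of Treatment effects and the last study aim both point to change. The halved estimate therefore describes one possible fit, not the stated analysis.

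It can also be said that a condensed article leaves time coding, interactions and covariates to a fuller protocol or analysis plan. That is fair, and the mere absence of those details would be no finding. But the article does name its treatment term, and it presents the slope as an addition tied to self-report measures. That wording fits the stated aim poorly for the CAPS-5.

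Third, a change contrast is valid in a randomised trial, so preferring baseline adjustment is a matter of efficiency. This stands, and the point is made on that footing: the gain over unadjusted change is 24.0% to 30.5%, much smaller than the gain over a plain group effect.

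Finally, a reader might infer from the balance check that baseline covariates are ruled out. The text does not say so. Whether to keep that check is a minor preference and does not affect this point.

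**Conclusion.** The point holds in a limited form. The named model term does not fix a contrast that matches the aim for CAPS-5 numbing, and a baseline-adjusted follow-up difference is at least as good on every reading considered. At 0.3 SD and ρ = 0.5 it has nearly three times the pre-post power of a plain group effect (30.5% against 10.8%) and about 6.5 percentage points more than unadjusted change. The dilution to half (pre-post) or two thirds (two follow-ups) arises only if a plain group effect is fitted with baseline among the outcome rows.

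A reader might also infer that the change rescues the sample size. It does not: at the planned 0.3 SD the adjusted analyses reach only about 31% to 43%. All figures rest on equal correlations between visits and complete data; dropout would lower them.

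**What to change.** Replace the pre-post model sentence with one that names the contrast. The treatment effect is the group difference at 12 weeks, with the 3-month difference secondary, from a mixed model with visit, group-by-visit and adjustment for the baseline value of the same outcome. A constrained longitudinal model with a common baseline mean in both arms is preferable. It keeps everyone with a baseline value in the analysis, which fits the intent-to-treat set described under Sample size calculation and power analyses. (The Randomization procedures section defines that set by first-session attendance, a separate matter to reconcile.) Apply the same contrast to CAPS-5, PCL-5 and ERNS numbing; slope tests for self-report measures can stay as supporting analyses.

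The cost is a change of wording. It needs no additional patients, visits or measures. The 85% power statement needs its own correction.
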